## Abstract

**Background:**

Prosthetic design for the use in primary total knee arthroplasty has evolved into designs that preserve the posterior cruciate ligament (PCL) and those in which the ligament is routinely sacrificed (posterior stabilized). In patients with a functional PCL the decision which design is chosen depends largely on the favour and training of the surgeon.

The objective of this study is to determine whether the patient's perceived outcome and speed of recovery differs between a posterior cruciate retaining total knee arthroplasty and a posterior stabilized total knee arthroplasty.

**Methods/Design:**

A randomized controlled trial will be conducted. Patients who are admitted for primary unilateral TKA due to primary osteoarthrosis are included when the following inclusion criteria are met: non-fixed fixed varus or valgus deformity less than 10 degrees, age between 55 and 85 years, body mass index less than 35 kg/m^2 ^and ASA score (American Society of Anaesthesiologists) I or II. Patients are randomized in 2 groups. Patients in the posterior cruciate retaining group will receive a prosthesis with a posterior cut-out for the posterior cruciate ligament and relatively flat topography. In patients allocated to the posterior stabilized group, in which the posterior cruciate ligament is excised, the design may substitute for this function by an intercondylar tibial prominence that articulates with the femur in flexion. Measurements will take place preoperatively and 6 weeks, 3 months, 6 months and 1 year postoperatively.

At all measurement points patient's perceived outcome will be assessed using the Western Ontario and McMaster Universities Osteoarthritis Index (WOMAC). Secondary outcome measures are quality of life (SF-36) and physician reported functional status and range of motion as determined with the Knee Society Clinical Rating System (KSS).

**Discussion:**

In the current practice both posterior cruciate retaining and posterior stabilized designs for total knee arthroplasty are being used. To date no studies have been performed determining whether there is a difference in patient's perceived outcome between the two designs. Additionally, there is a lack of studies determining the speed of recovery in both designs as most studies only determine the final outcome. This randomised controlled study has been designed to determine whether the patient's perceived outcome and speed of recovery differs between a posterior cruciate retaining total knee arthroplasty and a posterior stabilized total knee arthroplasty.

**Trial Registration:**

The trial is registered in the Netherlands Trial Registry (NTR1673).

## Background

Prosthetic design for the use in primary total knee arthroplasty has evolved into designs that preserve the posterior cruciate ligament (PCL) and those in which the ligament is routinely sacrificed (posterior stabilized). However, merely saving the PCL does not provide for normal knee kinematics unless a proper design is used and surgical technique is precise [1]. Posterior stabilized implants in which the ligament is excised may substitute for this function by an intercondylar tibial prominence that articulates with the femur in flexion, aiding in femoral roll-back [2]. In femoral roll-back there is a relative internal tibial rotation with flexion as the lateral condyle moves more posteriorly due to less constraint [3]. This femoral roll-back accounts for moving the tibiofemoral contact posteriorly by approximately 10 mm and represents approximately a 30 percent change in the lever arm of the quadriceps mechanism. This possible advantage is not present in the PCL-substituting designs [4].

In the current practice both designs are used. In patients whith a non functional PCL the posterior stabilised design is used. However, in patients with a functional PCL the decision which design is chosen depends largely on the favour and training of the surgeon. A limited amount of studies have been performed into the difference in outcome of the two designs. These studies are characterised by a small amount of patients, different outcome measures, poor randomisation and comparing designs of different manufacturers [5]. Range of motion was the only common outcome parameter; a meta-analysis showed a difference in range of motion and reproduction angle favouring posterior stabilized designs over PCL retention designs one year postoperatively. However, it is uncertain whether this observation is of clinical relevance [5]. To date, no studies have been performed determining whether there is a difference between designs in patient's perceived outcome. Additionally, there is a lack of studies determining the speed of recovery in both designs as most studies only determine the final outcome (e.g. after one year).

The primary objective of this randomized controlled trial is to examine whether there is a difference in patient's perceived outcome as determined with The Western Ontario and McMaster Universities Osteoarthritis Index (WOMAC) between a patient group receiving a posterior cruciate retaining total knee arthroplasty compared to a group receiving a posterior stabilized total knee arthroplasty.

## Methods

### Study design

A randomized controlled trial will be conducted. Patients that are scheduled for a primary total knee arthroplasty and apply to the inclusion criteria of the study are informed about the trial. After consent to participate, patients are allocated to receive either a posterior cruciate retaining total knee arthroplasty or a posterior stabilized total knee arthroplasty. The randomization procedure is based on sequentially numbered opaque sealed envelopes, produced by an external institution not involved in the selection, clinical care and evaluation of the patients. Two orthopaedic surgeons will perform the surgical procedure, therefore, block randomisation is used. The study design, procedures and informed consent are approved by the local Medical Ethical Committee (registration number 2007-23). The trial is registered in the Netherlands Trial Registry (NTR1673).

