### Sample Size

Sample size calculation is based on the primary outcome measure (WOMAC). A difference between the two groups of 15% is considered clinically relevant. With a standard deviation of 19.0 points, α = 0.05 and power of 80%, 55 patients are needed in each group. With an estimated drop-out of 10% in total 120 patients are needed, 60 patients in each group.

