### Statistical analysis

Descriptive statistics (means and standard deviations) will be used to describe the patient characteristics and outcome variables at the 5 measurement points.

A GLM repeated measures analysis will be used to determine whether there is a difference on the primary and secondary outcome variables between the two groups over time. A p-value of < 0.05 is considered significant.

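### Two surgeons are given as the reason for block randomisation, but the article does not say that blocks are formed within surgeon, and the stated model names no surgeon term

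*Protocol article*

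**What the plan says.** The Study design section of the protocol article gives the allocation method and its reason together: "Two orthopaedic surgeons will perform the surgical procedure, therefore, block randomisation is used". On the mechanics it says "The randomization procedure is based on sequentially numbered opaque sealed envelopes" and adds that an outside institution prepares them. It does not mention a separate series for each surgeon, stratification or a block size.

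The Statistical analysis section says "A GLM repeated measures analysis will be used to determine whether there is a difference on the primary and secondary outcome variables"; the comparison it names is of the arms across the visits. Surgeon is neither included nor excluded.

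The figures used below come from the Sample Size section: "With a standard deviation of 19.0 points, α = 0.05 and power of 80%, 55 patients are needed in each group", and "With an estimated drop-out of 10% in total 120 patients are needed, 60 patients in each group".

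**The concern.** In usual trial language, permuted blocks on one list keep the arm totals close as enrolment proceeds. They do not control how each surgeon's patients divide between the two designs. That happens only if the blocks are formed separately for each surgeon. The stated reason therefore supports the method on one reading and not on the other, and the article does not say which applies.

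The consequence depends on the reading:

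- **One blocked list.** Surgeon balance, which the plan gives as its reason for blocking, is left to chance.
- **Blocks within surgeon.** Surgeon is a design factor. A model without it counts between-surgeon variation as error, although the allocation has already removed that variation from the treatment comparison.

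What is at stake is some precision in the first case and some calibration and power in the second. A surgeon term in the model helps in both.

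**Working it through.** **Inputs from the Sample Size section:** 55 patients per arm for analysis, SD 19.0, α = 0.05, power 80%; 120 patients randomised, 60 per arm.

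**Assumptions, not in the article:** two-sided test; surgeon caseloads 50:50 (70:30 also tried); block sizes 4, 6 and 10; a gap D between surgeons of 5 or 10 WOMAC points. The calculation treats a single WOMAC comparison with a normal approximation.

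**The plan's own figure.** The article gives no figure for surgeon balance, so only the sample size can be reproduced. The base of the 15% difference is not stated, so the target in points has to be worked back from 55 per arm:

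19.0 × (1.960 + 0.842) × √(2/55) = 10.15 points.

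This equals 15% of a mean near 67.7. It is a derived figure and is used below only for power.

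**Standard error of the group difference:** 19.0 × √(2/55) = 3.62 points.

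**Reading A: one blocked list.**

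- SD of the between-arm difference in one surgeon's share: √(2 × 0.5 × 0.5 / 55) = 0.095.
- 95% chance range: ±1.96 × 0.095 = ±0.187, about ±19 percentage points.
- Shift at the edge of that range: 0.187 × 5 = 0.93 points; 0.187 × 10 = 1.87 points.
- Relative to the standard error: 0.93/3.62 = 0.26; 1.87/3.62 = 0.52.

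Simulation with 120 patients (5,000 runs per setting, ranges over the three block sizes) shows whether blocking on one list helps:

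| Caseload | Allocation | SD of share difference | Chance of a difference of 10 points or more | 95th percentile of the absolute difference |
|---|---|---|---|---|
| 50:50 | simple | 0.091–0.093 | 27–29% | 0.180–0.183 |
| 50:50 | one blocked list | 0.090–0.091 | 26–27% | 0.167–0.183 |
| 50:50 | blocks within surgeon | 0.011–0.016 | 0% | 0.017–0.033 |
| 70:30 | simple | 0.083–0.085 | 23–24% | 0.160–0.166 |
| 70:30 | one blocked list | 0.082–0.084 | 20–22% | 0.167 |
| 70:30 | blocks within surgeon | 0.011–0.017 | 0% | 0.023–0.033 |

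A single blocked list does about as well as simple randomisation. Blocks within surgeon all but remove the imbalance.

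**Reading B: blocks within surgeon, surgeon not in the model.** With equal caseloads, a gap D adds D²/4 to the residual variance: 6.25 for D = 5 and 25 for D = 10. The reported standard error includes this term, but the true variability of the treatment difference does not.

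- If 19.0 is the within-surgeon SD, the ratio of reported to true standard error is √(367.25/361) = 1.009 and √(386/361) = 1.034.
- If 19.0 is the total SD, the ratio is √(361/354.75) = 1.009 and √(361/336) = 1.037.
- Actual two-sided type I error, 2 × [1 − Φ(1.96 × ratio)], with 19.0 as the within-surgeon SD: 0.048 and 0.043.
- Power at 10.15 points, Φ(10.15/3.62 − 1.96 × ratio), same SD reading: 79.5% and 78.1%, against 80.0% with surgeon in the model.
- If 19.0 is the total SD, the corresponding powers are 80.2% against 80.7%, and 80.8% against 82.7%.

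On either reading of the SD, the model term is worth about half a percentage point of power for D = 5 and about two for D = 10.

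**The case against.** The strongest reply is that blocking on a factor, in the language of experimental design, means randomising within its levels. Since the article gives the two surgeons as the reason, blocks within surgeon is the reading under which its sentence makes sense. This stands. A reader might infer that the allocation fails to balance surgeons, but the article shows only that the point is left open.

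A second reply is that a journal article condenses the full protocol, and an analysis plan that is not shown may add surgeon to the model. This also stands. The analysis section names a model family and a comparison and does not rule surgeon out, so its silence alone would not be a finding. It matters here only because the article names surgeon as the reason for its allocation method. The structure of the allocation also has to be fixed before the envelopes are made, so a later analysis plan could not supply it.

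Third, a reader might take the Background statement that "the decision which design is chosen depends largely on the favour and training of the surgeon" as evidence that surgeon skill affects the outcome. It is not. It describes how a design is chosen in routine practice, whereas in the trial the design is randomised. The article gives no size for a surgeon effect on the WOMAC.

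Finally, the effect is small. Chance imbalance under one list does not bias the expected treatment effect, and the unadjusted test remains valid when between-surgeon variation is part of the SD. Under blocks within surgeon, the error is in the conservative direction. All of this is accepted.

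**Conclusion.** The point holds as a low-severity improvement. The article links two surgeons to block randomisation without the step that makes the link work, namely blocks formed within surgeon, and its stated model names no surgeon term.

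The two consequences cannot both apply, and the article does not settle which one does. They should not be read as two established defects, or as a threat to the trial's conclusion. Under one list the cost is unremoved chance variation, well inside the ordinary sampling error. Under blocks within surgeon it is a slightly conservative test.

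The sizes rest on assumed caseloads, an assumed surgeon gap of 5 to 10 points, a two-sided test, and a 10.15-point target worked back from the sample size. A smaller gap would shrink them, and with no gap they vanish. The case for the change is that it costs almost nothing and uses a factor the plan itself put forward.

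**What to change.** State in Study design that allocation uses permuted blocks within surgeon, and that the outside institution prepares one sealed envelope series for each surgeon. In Statistical analysis, include surgeon as a fixed effect in the repeated measures models for the primary and secondary outcomes.

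If enrolment has started, leave the envelopes as they are, report how they were prepared, and add the model term alone. It adjusts for surgeon under either reading.

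The cost is sorting the envelopes into two series and one between-patient degree of freedom. The sample size does not change. One caution applies: surgeons see which design they implant, so with a series each they could guess the end of a short fixed block. The block size should be kept from them or varied.

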### Study population

The study will be conducted at the Department of Orthopaedic Surgery of the Martini Hospital, which is a large teaching hospital in the city of Groningen, the Netherlands. Patients who are admitted for primary unilateral TKA due to primary osteoarthrosis are included when the following inclusion criteria are met: non-fixed fixed varus or valgus deformity less than 10 degrees, age between 55 and 85 years, body mass index less than 35 kg/m^2 ^and ASA score (American Society of Anaesthesiologists) I or II.

Patients with secondary osteoarthritis of the knee, rheumatic disease, a flexion less than 90 degrees, a flexion contracture over 10 degrees, peripheral neuropathy or a history of a cerebral vascular accident are excluded. Participation in the study is voluntary and informed consent is required. The inclusion period is planned from January 2008 to January 2010.

If perioperatively an insufficient posterior cruciate ligament is found, the patient will receive a posterior stabilized total knee prosthesis. Analyses will be done according to the intention-to-treat principle, with a sub-analysis excluding these conversions. As the incidence of an insufficient posterior cruciate ligament is higher in patients with secondary osteoarthritis of the knee, rheumatic diseases and a fixed varus or valgus deformity of over 10 degrees, these are exclusion criteria of our study.

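### Allocation appears to come before the PCL finding, so one-way conversions shrink the intention-to-treat difference, and the sample size makes no allowance for them

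*Protocol article*

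**What the plan says.** All references are to the protocol article.

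- **Background.** Knees whose PCL does not function get the posterior stabilized (PS) design. The open choice is elsewhere: "in patients with a functional PCL the decision which design is chosen depends largely on the favour and training of the surgeon".
- **Study design.** "After consent to participate, patients are allocated to receive either a posterior cruciate retaining total knee arthroplasty"; the alternative is the PS design. Allocation uses sealed envelopes. The text does not say when the envelope is opened relative to inspection of the ligament.
- **Study population.** "If perioperatively an insufficient posterior cruciate ligament is found, the patient will receive a posterior stabilized total knee prosthesis". The analysis follows intention-to-treat, and a sub-analysis leaves the converted patients out. Secondary osteoarthritis, rheumatic disease and larger fixed deformities are excluded because an insufficient PCL is more common there. No expected conversion rate is given.
- **Sample Size.** The target difference is a percentage without a reference value: "A difference between the two groups of 15% is considered clinically relevant". The other inputs (power 80%, α 0.05, SD 19.0) lead to 55 evaluable patients per arm. The only inflation is for patients lost: "With an estimated drop-out of 10% in total 120 patients are needed, 60 patients in each group". Conversions do not enter the calculation.

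**The concern.** Crossover can run in one direction only, from retaining to PS. A knee with an insufficient PCL receives a PS implant whichever arm it is in, so it adds nothing to the contrast between designs. Under intention-to-treat it still counts in its arm and pulls the two means together.

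Two things are at stake. The trial has less chance of detecting the difference it was sized for. And a null result is harder to interpret for knees with a functional PCL, the group for which the Background says the choice of design is open. The plan foresees conversions, yet its sample size covers only drop-out.

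**Working it through.** **1. Order of events.** A conversion kept in its allocated arm can exist only if allocation came before the PCL finding. The sequence is therefore implied by Study design and Study population read together; neither section states it.

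**2. Effect of conversions on the intention-to-treat difference.** Let c be the share of knees with an insufficient PCL, equal in expectation in both arms by randomisation. Assume such knees do equally well with a PS implant in either arm.

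- Retaining arm mean: (1 − c) × (sufficient knees, retaining) + c × (insufficient knees, PS)
- PS arm mean: (1 − c) × (sufficient knees, PS) + c × (insufficient knees, PS)
- Difference: (1 − c) × effect in sufficient knees

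**3. The sub-analysis.** Leaving out conversions removes the last term from the retaining arm only. The difference becomes: effect in sufficient knees + c × (sufficient minus insufficient knees, both with PS). The second part vanishes only if PCL status does not affect outcome. The comparison is no longer between randomised groups.

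**4. The plan's own figure.** Inputs from Sample Size: SD 19.0, α 0.05 (two-sided assumed), power 80%, 55 per arm. The 15% has no reference value, so 55 cannot be derived directly from the stated inputs.

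- Read as 15 points: n = 2 × 19² × (1.960 + 0.842)² / 15², which gives 26 per arm, not 55.
- Solved backwards from 55: difference = 19 × √(2/55) × (1.960 + 0.842) = 3.623 × 2.802 = 10.15 points, which is 15% of about 67.7.

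The difference of 10.15 is therefore an inferred input.

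**5. Slack in the drop-out allowance.** 60 × 0.9 = 54 per arm, with power 79.3% at 10.15 points. Nothing is left over for conversions.

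**6. Power with conversions.** Power = Φ(10.15 × (1 − c) / 3.623 − 1.96) at 55 per arm. Evaluable n per arm to restore 80% = 55 / (1 − c)², rounded up. The values of c are assumptions.

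| c | Difference under ITT (points) | Power at 55 per arm | n per arm for 80% |
|---|---|---|---|
| 0% | 10.15 | 80.0% | 55 |
| 2% | 9.95 | 78.4% | 58 |
| 5% | 9.64 | 75.9% | 61 |
| 10% | 9.14 | 71.3% | 68 |
| 20% | 8.12 | 61.1% | 86 |

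Power drops below 78% once c exceeds about 2.5%. Adding the extra variance from mixing converted and unconverted knees changes little: 70.7% instead of 71.3% at 10%, and 60.1% instead of 61.1% at 20%.

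**The case against.** The strongest case for the plan is that it has dealt with conversions. It names them, chooses eligibility criteria to keep them rare, analyses by intention-to-treat and adds a sub-analysis. Comparing planned implants, with conversion as part of the strategy, is a legitimate question, and the primary objective and eligibility criteria are not restricted to a functional PCL. With an unknown and deliberately lowered rate, the loss may be negligible.

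Much of this stands. Intention-to-treat is sound and is not criticised here. The exclusions do lower c. But the article says only that insufficiency is more common in the excluded groups, and the conversion rule shows that cases are still expected. The sub-analysis does not restore the comparison (step 3). If PCL sufficiency were also recorded in the PS arm, the matching knees could be left out of both arms; the article does not say whether it is.

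A second objection is that the planned analysis is a repeated-measures GLM over five time points, not one comparison of two means. This also stands. The power of that analysis depends on correlations that are not given, so the absolute percentages need not carry over. The proportional shrinkage of the difference does carry over, for conversions that affect every postoperative time point alike.

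A reader might also infer that the surgeon judges sufficiency knowing the allocation, which would let the allocation influence who converts. The documents do not support this as fact: they do not say when the surgeon learns the allocation. It is at most an inference from the implied sequence.

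**Conclusion.** The point holds in a limited form. Allocation before the PCL finding is implied, the conversions it creates reduce the intention-to-treat difference by the factor (1 − c), and the sample size contains nothing for them.

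The size cannot be fixed from the document. It rests on an assumed conversion rate, a difference of 10.15 points solved backwards from 55 per arm, two-sided α and a simple two-mean comparison. On that basis the loss is trivial at about 2% conversions or less, about 4 percentage points at 5%, 9 at 10% and 19 at 20%.

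A reader might conclude that the trial is clearly underpowered. The documents do not support that, because they give no conversion rate. If the difference really were 15 points, 55 per arm would keep 80% power up to about 32% conversions (1 − 10.15/15), but that reading does not fit the stated sample size. What is supported is that the stated 80% assumes no conversions, while the plan expects some, and that a cheap change in sequence would improve both the power and the answer for knees with a functional PCL.

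**What to change.** **Preferred.** Open the existing sealed envelope in theatre, after PCL sufficiency has been assessed and recorded, and randomise only patients whose PCL is recorded as sufficient. Any conversion that still arises later stays in its arm under intention-to-treat. Sufficiency is then judged before the allocation is revealed, and c should fall close to zero.

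Cost: slightly more patients must be consented, since some will not be randomised. Both designs must be available for every case. The conversion rule already requires a PS implant to be available for patients in the retaining arm, but nothing at present requires a retaining implant for patients allocated to PS.

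**If that is not feasible.** Keep the sequence and restate power as a range over assumed conversion rates, including low ones such as 2%, with the difference in points written out. This costs a sentence or two.

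Neither option changes the clinical rule for an insufficient PCL.

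### The sub-analysis without conversions drops PCL-insufficient knees from the retaining arm only, so it is not a randomised comparison and is biased if PCL insufficiency is related to outcome

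*Protocol article*

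**What the plan says.** Patients are randomised between two implants. Under Study design, "patients are allocated to receive either a posterior cruciate retaining total knee arthroplasty or a posterior stabilized total knee arthroplasty". Study population then sets a rule for a finding made during the operation: "If perioperatively an insufficient posterior cruciate ligament is found, the patient will receive a posterior stabilized total knee prosthesis". The next sentence fixes the analysis sets: "Analyses will be done according to the intention-to-treat principle, with a sub-analysis excluding these conversions".

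Two further statements bear on the point. The Methods/Design part of the Abstract describes the stabilized arm: "In patients allocated to the posterior stabilized group, in which the posterior cruciate ligament is excised". Study population also explains some of the eligibility criteria: "As the incidence of an insufficient posterior cruciate ligament is higher in patients with secondary osteoarthritis of the knee, rheumatic diseases", together with larger fixed deformities, and for that reason these patients are not entered.

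**The concern.** The rule for the sub-analysis looks symmetrical but acts on one arm. A PCL-insufficient knee allocated to the retaining design is converted and dropped. The same kind of knee allocated to the stabilized design gets its allocated implant, is not a conversion, and stays in. What remains is a retaining group selected for a sufficient PCL against an unselected stabilized group, and randomisation no longer makes the two comparable.

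The Background and Discussion pose the design question for patients whose PCL works. The sub-analysis appears to address exactly those patients and will be read beside the intention-to-treat (ITT) result. If insufficient knees do worse, it tilts towards the retaining design even when the implants are equivalent. If they do better, it tilts the other way.

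**Working it through.** **Inputs from the article.** SD 19.0 points and 55 patients per arm (Sample Size). Conversion is possible in the retaining arm only (Study design and Study population read together). The article states no figure for conversions or for the sub-analysis, so there is none to reproduce.

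**Inputs assumed.** c is the share of knees with an insufficient PCL, equal in both arms by randomisation. g is the WOMAC deficit of insufficient against sufficient knees when both carry the stabilized implant, with higher scores better. Where the contrast is on change over time, g is the deficit in change.

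**Derivation.** Let m be the mean of sufficient knees with the stabilized implant, and d the true effect of the retaining design in sufficient knees.

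- Retaining arm after the exclusion: m + d
- Stabilized arm, all patients: (1 − c)·m + c·(m − g) = m − c·g
- Planned sub-analysis: (m + d) − (m − c·g) = d + c·g. The bias is c·g whatever the value of d.
- ITT: insufficient knees receive the same implant in both arms and cancel, leaving (1 − c)·d. This is zero when d is zero.
- Sufficient knees in both arms: (m + d) − m = d
- ITT divided by (1 − c): d

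**Scale.** The standard error of a difference with 55 per arm is 19 × √(2/55) = 3.62 points.

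**Size.** The last two columns come from a simulation of the planned sub-analysis with d = 0, 55 per arm, SD 19 and 20,000 trials per setting (nominal level 0.05).

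| c | g | c × g | c × g ÷ 3.62 | simulated mean difference | simulated type I error |
|---|---|---|---|---|---|
| 5% | 5 | 0.25 | 0.07 | 0.24 | 0.053 |
| 5% | 10 | 0.50 | 0.14 | 0.52 | 0.052 |
| 10% | 5 | 0.50 | 0.14 | 0.52 | 0.052 |
| 10% | 10 | 1.00 | 0.28 | 1.05 | 0.059 |
| 20% | 10 | 2.00 | 0.55 | 2.01 | 0.082 |
| 20% | 15 | 3.00 | 0.83 | not run | not run |

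In the five simulated settings, ITT and the exclusion of insufficient knees from both arms each gave mean differences within 0.04 points of zero.

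**Against the trial's target difference.** The article says "A difference between the two groups of 15% is considered clinically relevant" without naming the base of the percentage. Working back from 55 per arm, SD 19, 80% power and a two-sided 5% test gives (1.960 + 0.842) × 3.62 = about 10.15 points, which would be 15% of 10.15/0.15 = 67.7. On that inferred figure, a bias of 1.0 point is about 10% of the target and 3.0 points about 30%.

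**Precision of the alternatives at c = 10%.** Restricting both arms leaves about 49.5 per arm: 19 × √(2/49.5) = 3.82 points. The rescaled ITT estimate has 3.62/0.90 = about 4.03 points, treating c as known.

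**The case against.** The strongest reply is that little depends on this analysis. ITT is the stated principle, and neither the objective nor the sample size rests on the sub-analysis. The eligibility criteria are chosen to keep PCL insufficiency rare, so c may be small. The gap g may be small too: every stabilized knee loses its PCL, and the Intervention section says the cam and post take over its function, so prior PCL status might matter little once that implant is in. No passage says that insufficiency predicts WOMAC. All of this stands and limits the size of the problem. It does not make a one-arm exclusion a randomised comparison, and insufficiency could still mark more advanced disease.

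It can also be said that the one-arm reading is inferred. It is, but a patient who receives the allocated implant has not been converted, and no other reading fits the sentence well.

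Some stronger readings are tempting and are not supported:

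- A reader might infer that the surgeon judges the PCL knowing the allocation. The article does not say when the envelope is opened relative to that judgement, and the argument does not need it.
- A reader might take a failure to record PCL status in the stabilized arm as a fault. A condensed article may leave that to the full protocol. The criticism is of the exclusion rule it does state.
- A reader might conclude that any disagreement with ITT would be uninterpretable. The number of conversions will be known, so the distortion can be bounded for a range of g.

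**Conclusion.** The concern holds as a defect of the sub-analysis alone. As worded, it compares PCL-selected retaining patients with unselected stabilized patients, and its bias is c × g, which vanishes only if c or g is zero. Under assumed values of 5–10% and 5–10 points, the bias is 0.25–1.0 point, at most about 0.28 of a standard error, with little effect on the error rate. Three points needs 20% insufficient knees and a 15-point deficit, and the article supports neither. The figure of about 30% of the target difference belongs to that corner and also rests on a back-calculated 10.15 points, so it should not be quoted as the expected effect.

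The direction favours the retaining design only if insufficient knees do worse. A reader might infer that the trial's main result is compromised. It is not, because ITT keeps all randomised patients in their allocated arms. Severity is moderate: the bias is probably small, but the rule is wrong as stated and cheap to correct, and PCL status in the stabilized arm cannot be recovered after resection.

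**What to change.** 1. Record PCL sufficiency in every patient of both arms, by the same written criterion, before the PCL is resected.
2. Redefine the sub-analysis as patients with a sufficient PCL in both arms, analysed by allocation.
3. If that record is not available, replace the exclusion by a complier-average causal effect: the ITT difference divided by one minus the retaining-arm conversion proportion, with randomisation as the instrument. It assumes that allocation does not affect the outcome of insufficient knees, which receive the same implant either way, and that no stabilized-arm patient receives the retaining design. The article foresees no such crossover, and the planned blinding of patients supports the first assumption.
4. Keep ITT primary, label the sub-analysis supportive, and report the number of conversions.

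The cost is one item on the operation form and a sentence in the analysis section. The complier estimate needs no new data, but its interval is somewhat wider (about 4.03 against 3.62 points of standard error at c = 10%). Because it rescales ITT, it adds no independent evidence. No extra patients are needed, and the conversion rule itself is left as it is.
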